### Outcome measures

2.12

#### Primary outcome

2.12.1

The primary outcome is the change in limb motor function in stroke patients before and after treatment, assessed using the simplified Fugl-Meyer Assessment (FMA) scale. Limb motor function impairment will be quantified by evaluating upper/lower extremity functions, balance, sensation, and joint range of motion. The scale comprises 50 items (33 for upper limbs, 17 for lower limbs), with higher scores indicating better functional activity.

#### Secondary outcome

2.12.2

##### Balance ability

2.12.2.1

The static and dynamic balance ability of patients will be assessed using the Berg Balance Scale (BBS). The scale includes 14 items and uses a 5-point rating system. Each item is scored 0–4 according to the patient’s performance, for a total of 56 points, with higher scores indicating better balance ability.

##### Sensory function

2.12.2.2

The degree of sensory impairment will be assessed using the sensory scale of the Fugl-Meyer Assessment (FMA-S). The scale evaluates light touch and proprioception with 12 items (2 points each), totaling 24 points, with higher scores indicating better sensory function.

##### Muscle tone

2.12.2.3

Limb muscle spasticity will be evaluated using the Modified Ashworth Scale (MAS) by assessing the resistance encountered during passive muscle stretching. The scale has 6 levels, ranging from no increase in muscle tone to rigidity. Level 0 indicates normal joint mobility, while level 4 indicates the most severe spasticity, with the joint immovable.

##### Activities of daily living

2.12.2.4

The impact of limb dysfunction on daily living activities will be assessed using the Modified Barthel Index (MBI). The scale includes 10 items, each scored 0–10, totaling 100 points, with higher score indicating better independence in daily life for stroke patients.

##### TCM syndrome score

2.12.2.5

TCM syndrome scoring scale is drawn in accordance with the “Diagnostic and Efficacy Evaluation Criteria for Stroke” (24). The scale quantifies clinical symptoms and signs related to phlegm-turbidity and blood stasis in stroke patients through TCM syndrome scoring, totaling 14 items, with higher score indicating more severe symptom.

##### EEG data collection

2.12.2.6

Patients will undergo EEG examination before and after treatment, respectively. EEG recording will be conducted in a dimly lit and quiet environment to avoid visual and auditory distractions. Patients are required to avoid caffeinated beverages, sedatives, and stimulants for three days prior to the examination. They should also ensure 7.5 h of sleep before the test and avoid fatigue, hunger, and hypoglycemia. During the examination, they should stay conscious, keep their eyes closed, remain relaxed, and refrain from feeling tense or anxious. The study will employ the 32 U-type digital electroencephalogram/brain electrical activity mapping (EEG/BEAM) instrument, with electrodes placed according to the international 10–20 system (refer to Figure 4). In the unipolar lead method, bilateral earlobes (A1, A2) are selected as the reference electrodes to record the potential difference between the active electrodes and the reference electrodes. The lead arrangement is as follows: FP1-A1, FP2-A2, F3-A1, F4-A2, C3-A1, C4-A2, P3-A1, P4-A2, O1-A1, O2-A2, F7-A1, F8-A2, T3-A1, T4-A2, T5-A1, T6-A2. The bipolar lead method records the potential difference between two adjacent electrodes, anterior and posterior, in symmetrically paired regions of the left and right hemispheres. The lead arrangement is as follows: FP1-F3, F3-C3, C3-P3, P3-O1, FP2-F4, F4-C4, C4-P4, P4-O2, FP1-F7, F7-T3, T3-T5, T5-O1, FP2-F8, F8-T4, T4-T6, T6-O2. Parameter settings: sensitivity 10 μv/mm, time base 30 mm/s, time constant 0.3, high-pass filter 70 Hz, low-pass filter 0.53 Hz. Routine eye-opening/closing evoked test will be conducted during recording, with a duration of 20 min. An independent researcher will analyze EEG data, calculating the frequency and amplitude of background brainwave patterns in each hemisphere and abnormal waveforms in lesioned regions. EEG data will be collected using the XLTEK neuroworks EEG system.

**Figure 4 fig4:**
[figure not shown]
Electrode positions in the international 10–20 system.

##### EEG data processing

2.12.2.7

EEG signals collected from electrodes placed at different head regions are filtered to remove interference signals with frequencies below 0.5 Hz and above 30 Hz. Independent component analysis (ICA) is applied to eliminate non-cerebral interferences from the EEG data, such as electrooculography (EOG) artifacts and electromyography (EMG) signals. After amplified, the processed signals are input into a computer’s analog-to-digital converter (ADC), where the waveform signals are transformed into digital information and stored in the computer’s memory. Fast Fourier Transform (FFT) will analyze voltage variables at different time phases to process the power spectra across various frequency bands. The full-band spectral power plot is displayed with a frequency resolution of 1 Hz per step, and power plots are generated for the four frequency bands: delta (1–4 Hz), theta (4–8 Hz), alpha (8–13 Hz), and beta (13–30 Hz). The grayscale images will be converted into color bands, their grayscale levels will be numerically quantified, and a grayscale scale will be generated for analysis using BESA (Brain Electrical Source Analysis, BESA) software.

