##### Coherence analysis

2.12.2.8

Coherence is an index used in EEG analysis to measure signal synchrony between two brain regions, reflecting the degree of functional connectivity between them. The coherence C*_xy_* (*f*) between two EEG signals *x* and *y* from different electrodes at frequency *f* is calculated using the following formula:

$$C_{\mathrm{xy}}(f)=\frac{|P_{\mathrm{xy}}(f)|2}{P_{\mathrm{xx}}(f).P_{\mathrm{yy}}(f)}$$

*P_xx_* (*f*) and *P_yy_* (*f*) represent the power spectral densities of signals *x* and *y*, respectively, while *P_xy_* (*f*) is the cross-spectral density between *x* and *y*, all of which are estimated using the Welch method. Coherence ranges from 0 to 1, with higher values indicating greater similarity in phase and amplitude between EEG signals, among which, a value of 1 indicates complete synchronization, while 0 indicates complete desynchronization. This study will calculate coherence in the alpha and beta bands, designating the M1 region (primary motor cortex) on the ipsilesional or contralesional side of the lesion as the seed region, and will calculate coherence values between the seed region and all other regions. In the 32-electrode layout of the international 10–20 system, the M1 seed region is defined as C3 (for the left hemisphere M1) or C4 (for the right hemisphere M1). When the infarct lesion is located in the right hemisphere, the data will be flipped along the midline to standardize the analysis hemisphere. For normally distributed data, two independent-samples t-test will be conducted, while for non-normally distributed data, non-parametric Wilcoxon test will be applied to compare Coherence differences between the two groups. Additionally, Cohen’s *d* will be calculated to quantify the effect size, and the Bonferroni correction will be employed to control the false positive rate associated with multiple comparisons.

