
Outcome measures include the simplified Fugl-Meyer Assessment for motor function, the Berg Balance Scale, the Fugl-Meyer Assessment for sensory function, the Modified Ashworth Scale, the Modified Barthel Index, and TCM syndrome scoring scale, which are used to comprehensively evaluate the efficacy of the “simultaneous treatment of phlegm and blood stasis” acupuncture therapy based on syndrome differentiation on improving limb mobility, balance, sensation, muscle tone, activities of daily living, and TCM-related symptoms/signs in ischemic stroke patients with hemiplegia. Resting-state EEG is highly sensitive to cerebral metabolic and neurological functional abnormalities, serving as an important method for assessing post-stroke brain function (38). Commonly used frequency bands in EEG include alpha, beta, theta, and delta waves. Alpha wave activity during rest reflects the level of consciousness and visual attention (39). With a frequency range of 8–13 Hz, alpha waves are brain rhythms involved in various functions, ranging from sensorimotor processing to memory formation (40). Research indicates a linear relationship between reduced synchrony of alpha wave oscillations among brain regions and cognitive/motor function impairments in stroke patients (41). Beta waves, oscillating at 13–30 Hz, are crucial rhythms in cortical activity, closely related to motor control and sensorimotor integration (42), with their generation involving the synergistic action of pyramidal and inhibitory neurons (43). Research has found that beta wave coherence can serve as a marker for cortical functional plasticity after stroke (42). Delta waves are low-frequency waves with frequencies ranging from 1–4 Hz, and can be detected during slow-wave sleep and execution of cognitive tasks (44). Theta waves, with frequencies in the 4–8 Hz range, have been extensively studied in emotional and cognitive domains. Recent research has found that perturbation during seated movements can evoke differential theta-band responses in the anterior cingulate cortex and supplementary motor areas (45). In this study, we will employ EEG to record and analyze the frequency, amplitude, and spectral power of delta, theta, alpha, beta waves. We will designate the M1 region as the seed region and calculate the coherence of alpha and beta waves between the seed region and other regions. By observing changes in neuronal oscillation frequencies, electrical activity intensity, and functional connectivity across different brain regions before and after treatment, we aim to explore the neurophysiological mechanisms, by which acupuncture improve limb function in stroke patients, and screen EEG-based biomarkers with predictive value.

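### EEG spectral power is planned to be read from the grey levels of power-map images, although the FFT already gives band power as numbers

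*Protocol article*

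**What the plan says.** Section 2.12.2.7 of the protocol article sets out the processing chain for spectral power. After filtering and artefact removal, "Fast Fourier Transform (FFT) will analyze voltage variables at different time phases to process the power spectra across various frequency bands". Next, "power plots are generated for the four frequency bands" (delta, theta, alpha and beta). The grey images are then recoloured in bands, "their grayscale levels will be numerically quantified, and a grayscale scale will be generated for analysis", and BESA is named as the software.

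The Discussion (section 3) says the trial will "record and analyze the frequency, amplitude, and spectral power of delta, theta, alpha, beta waves". Section 2.12.2.7 is the only place that describes how spectral power becomes an analysed quantity.

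The other EEG measures take different routes. Section 2.12.2.6 (EEG data collection) has an independent researcher "calculating the frequency and amplitude of background brainwave patterns in each hemisphere and abnormal waveforms in lesioned regions". Section 2.12.2.8 (Coherence analysis) builds coherence from power and cross-spectral densities, "all of which are estimated using the Welch method". Neither mentions map images.

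The EEG measures stand under the secondary outcomes. Section 2.16 (Statistical analysis) adds subgroup analyses of EEG indicators by infarct location and an ROC analysis of EEG as a predictor of acupuncture response. It does not say which EEG measures enter these.

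**The concern.** The FFT output is already a number for each electrode and frequency. Drawing it as an image and reading the image back adds a step that can lose information and cannot add any. A grey level stands in for power only if the scale is fixed, has a known relation to power, covers the whole range without saturating, and is the same for every patient and both visits. Section 2.12.2.7 states none of these conditions.

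This is a step that the article states, not a detail that it leaves out: the grey scale is produced for the purpose of analysis. If the step is carried out as written, the comparison of power between arms and between visits, and any biomarker search that uses power, would partly reflect display settings. Under some settings, a general rise or fall in power would shrink or disappear.

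**Working it through.** The documents give no figure for EEG power, so there is nothing of the plan's own to reproduce. The check has two parts.

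**1. Which EEG measures pass through the image step**

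| Measure | Where described | How obtained |
|---|---|---|
| Spectral power, four bands | 2.12.2.7 | FFT, then power maps, then grey levels |
| Background frequency and amplitude | 2.12.2.6 | calculated by an independent researcher; no image step |
| Coherence, alpha and beta | 2.12.2.8 | Welch spectral densities |

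Only spectral power is affected. Section 2.12.2.8 already requires numeric power spectral densities for coherence, so numeric spectral output is within the trial's means.

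**2. What a grey level does to a known change in power**

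All inputs here are assumptions chosen for illustration.

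- Power at five sites before treatment: 2, 4, 8, 12, 20 (arbitrary units).
- True change: a uniform rise of 50%, giving 3, 6, 12, 18, 30. The true ratio of means is 1.50.
- Eight-bit grey level: g = round(255 × min(power / S, 1)), where S is the top of the scale and exact halves round to the even integer.

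| Scale | Grey levels before (sum) | Grey levels after (sum) | Ratio |
|---|---|---|---|
| Fixed and wide, S = 40 | 13, 26, 51, 76, 128 (294) | 19, 38, 76, 115, 191 (439) | 439/294 = 1.49 |
| Fixed but saturating, S = 20 | 26, 51, 102, 153, 255 (587) | 38, 76, 153, 230, 255 (752) | 752/587 = 1.28 |
| Each map's own maximum, S = 20 then 30 | 26, 51, 102, 153, 255 (587) | 26, 51, 102, 153, 255 (587) | 587/587 = 1.00 |

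The same 50% rise is recorded as 49%, 28% or 0%. On the wide fixed scale the only loss is rounding, and it is trivial. On the saturating scale the strongest site cannot rise above 255. With per-map scaling, S grows by the same factor as the power and cancels it, so a uniform change of any size gives 1.00. Such a map keeps the relative pattern across sites and loses the overall level.

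**The case against.** The strongest reply is that a grey level is only rescaled power. The scale that the article says will be generated could be a calibrated key linking level to power, and the Discussion does call the analysed quantity spectral power. With a fixed, wide scale the working gives 1.49 for a true 1.50, so serious harm needs an unfavourable scale that no passage states. Map scaling is also a software setting that an article may leave to the full protocol. Much of this stands: the documents do not show that power will be distorted, only that its fidelity hangs on a setting they do not fix. It does not rescue the step itself. Even in the best case, reading values back from an image gains nothing over the numbers that produced it.

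Two stronger readings are tempting, and the documents do not support them.

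- *That the whole EEG outcome is a display value.* Frequency, amplitude and coherence are described without the image step. Coherence is also the measure for which section 2.12.2.8 names the between-group test, the effect size and the multiplicity correction.
- *That eyes-open and eyes-closed data are mixed in the analysis.* Section 2.12.2.6 tells patients that "they should stay conscious, keep their eyes closed, remain relaxed" and also says "Routine eye-opening/closing evoked test will be conducted during recording, with a duration of 20 min". Both states therefore occur in the recording, and a reader might infer that they are pooled. No passage says so. The eyes-closed instruction and the Discussion's reference to resting-state EEG fit an eyes-closed analysis with a separate reactivity check. Epoch selection is a detail that an article may leave to the full protocol or analysis plan.

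**Conclusion.** The point holds for spectral power alone. Section 2.12.2.7 commits the trial to quantifying power from image grey levels when numeric band power is already available, and it does not fix the scale that decides whether the result is faithful. With the assumed site powers and a true uniform ratio of 1.50, the recorded ratio runs from 1.49 (fixed wide scale) through 1.28 (saturating scale) to 1.00 (per-map scaling). These figures show what can happen under each scale. They do not estimate what will happen in this trial.

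The consequence is limited to a secondary measure used for mechanism and possibly for biomarker screening. The primary Fugl-Meyer outcome and the sample size do not depend on it. The change is worth making because it removes an avoidable source of measurement error at almost no cost.

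**What to change.** Replace the grey-level sentence in section 2.12.2.7 with:

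> Band power (absolute and/or relative) for delta, theta, alpha and beta will be exported numerically from the FFT for each electrode and used for all analyses; maps are for illustration only.

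The cost is a wording change and a numeric export in place of image quantification, which makes the analysis simpler. The trial is already recruiting, so the change should be settled before any EEG power is analysed. If the raw recordings are kept (an assumption), patients already recorded can be processed in the same way.

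Optionally, the same edit could name the eyes-closed epochs that enter the power and coherence analyses. That would be a clarification and does not correct an error.

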##### Coherence analysis

2.12.2.8

Coherence is an index used in EEG analysis to measure signal synchrony between two brain regions, reflecting the degree of functional connectivity between them. The coherence C*_xy_* (*f*) between two EEG signals *x* and *y* from different electrodes at frequency *f* is calculated using the following formula:

$$C_{\mathrm{xy}}(f)=\frac{|P_{\mathrm{xy}}(f)|2}{P_{\mathrm{xx}}(f).P_{\mathrm{yy}}(f)}$$

*P_xx_* (*f*) and *P_yy_* (*f*) represent the power spectral densities of signals *x* and *y*, respectively, while *P_xy_* (*f*) is the cross-spectral density between *x* and *y*, all of which are estimated using the Welch method. Coherence ranges from 0 to 1, with higher values indicating greater similarity in phase and amplitude between EEG signals, among which, a value of 1 indicates complete synchronization, while 0 indicates complete desynchronization. This study will calculate coherence in the alpha and beta bands, designating the M1 region (primary motor cortex) on the ipsilesional or contralesional side of the lesion as the seed region, and will calculate coherence values between the seed region and all other regions. In the 32-electrode layout of the international 10–20 system, the M1 seed region is defined as C3 (for the left hemisphere M1) or C4 (for the right hemisphere M1). When the infarct lesion is located in the right hemisphere, the data will be flipped along the midline to standardize the analysis hemisphere. For normally distributed data, two independent-samples t-test will be conducted, while for non-normally distributed data, non-parametric Wilcoxon test will be applied to compare Coherence differences between the two groups. Additionally, Cohen’s *d* will be calculated to quantify the effect size, and the Bonferroni correction will be employed to control the false positive rate associated with multiple comparisons.

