### Inclusion criteria

2.4

Patients who meet diagnostic criteria of Western medicine for ischemic stroke, combined with CT or MRI;Patients who meet diagnostic criteria for phlegm and blood stasis obstructing meridians in TCM syndrome;Aged between 30 and 80, inclusive;First occurrence, or those with a previous stroke but without sequelae;1 week to 3 months after the onset of stroke;Lesion in one cerebral hemisphere with unilateral hemiplegia, Brunnstrom stage II-IV;Right handedness;Patients with clear minds, clinically stable conditions, and limb dysfunction caused by stroke.

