### Randomization and allocation concealment

2.8

The grouping will be performed using a completely random method. The random allocation sequence will be generated through an online randomization tool Med Sci (http://tools.medsci.cn/rand) and managed by an independent researcher. Stroke patients who meet the inclusion criteria will be randomized into the acupuncture group or the sham acupuncture group in a 1:1 ratio after signing the informed consent. Cards printed with information on the allocated groups will be placed in opaque envelopes. Patients will receive envelopes sequentially according to the order of inclusion. An acupuncturist will open envelopes prior to treatment and conduct the corresponding treatment. The randomization process will be carried out by an independent researcher who is not involved in the recruitment, evaluation, and intervention.

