### Statistical analysis

2.16

All data will be analyzed using SPSS 27.0 statistical software. In accordance with the intention-to-treat (ITT) principle, patients who have received at least one treatment session will be included in the analysis. Basic information, baseline data, and efficacy evaluation will be analyzed using both the full analysis set (FAS) and per-protocol set (PPS). In case of inconsistent results between the two datasets, further analysis and evaluation will be conducted. Missing data will be imputed using multiple imputation method. For continuous outcomes, post-treatment data are presented as mean±SD if normally distributed with equal variances; otherwise, they are presented as median (IQR). ANCOVA will be used to adjust for baseline values and confounders (e.g., age, gender, revascularization therapy status), with adjusted mean differences and 95% CIs reported. For categorical data, frequencies and percentages will be presented, and potential confounders will be screened via univariate analysis before constructing stepwise logistic regression models to adjust for confounders and report odds ratios with 95% CIs, followed by validation of the model’s goodness of fit. Further, patients will be grouped based on infarction location to analyze EEG indicators in each subgroup. Receiver operating characteristic (ROC) curve analysis will be conducted to evaluate the predictive value of EEG as an efficacy indicator for acupuncture response, with the area under the curve (AUC) and 95% CI reported. For correlation analysis, Pearson correlation will be applied to normally distributed continuous data, while Spearman correlation will be used for ordinal data. All data analysis will be conducted using two-tailed tests with a significant level of 5%.

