
There are still some limitations in the design of this study: (1) the study does not restrict the infarction sites of included patients to the same hemisphere or specific locations, leading to increased heterogeneity in EEG signals; (2) the study duration is short, and there is a lack of follow-up observation after treatment course, making it difficult to ascertain the long-term efficacy of acupuncture therapy; (3) due to the treatment characteristics of acupuncture, it is challenging to implement blinding for acupuncturists and patients; (4) a multicenter study is not designed, making it impossible to verify the general applicability of the study across different populations and medical conditions. Hence, based on this study, we will further conduct multicenter, large-sample, long-term follow-up clinical trials for ischemic stroke patients in recovery stage.

Collectively, the primary objective of this clinical trial is to evaluate the efficacy and safety of the “simultaneous treatment of phlegm and blood stasis” acupuncture therapy in improving limb motor impairment in ischemic stroke patients with hemiplegia using functional scales, while exploring its underlying electrophysiological mechanisms through EEG. By conducting this clinical study, we expect to provide reliable scientific evidence for the clinical application of acupuncture therapy featuring characteristic acupoint combinations based on TCM syndrome differentiation in the field of neurological rehabilitation for ischemic stroke.

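### The between-arm coherence test is unadjusted although left- and right-lesion EEGs are pooled after mirroring; adding lesion side to the planned ANCOVA would gain precision at almost no cost

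*Protocol article*

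**What the plan says.** All references are to the protocol article.

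- **Eligibility (2.4).** Patients must satisfy "Right handedness" and "Lesion in one cerebral hemisphere with unilateral hemiplegia, Brunnstrom stage II-IV". A lesion on either side qualifies. No reason is given for the handedness rule.
- **Seed and mirroring (2.12.2.8).** The seed is M1 on the lesioned or the opposite side, and "the M1 seed region is defined as C3 (for the left hemisphere M1) or C4 (for the right hemisphere M1"). For right-sided lesions: "When the infarct lesion is located in the right hemisphere, the data will be flipped along the midline to standardize the analysis hemisphere".
- **Test (2.12.2.8).** "For normally distributed data, two independent-samples t-test will be conducted, while for non-normally distributed data, non-parametric Wilcoxon test will be applied" to compare coherence between the arms, with a Bonferroni correction.
- **Allocation (2.8).** "The grouping will be performed using a completely random method". No stratification factor is named.
- **General analysis (2.16).** "ANCOVA will be used to adjust for baseline values and confounders (e.g., age, gender, revascularization therapy status"). The covariate list is open and does not name lesion side. The section also plans EEG analyses in subgroups by infarct location, without saying whether location means hemisphere.
- **Limitations (Discussion).** Limitation (1) is that "the study does not restrict the infarction sites of included patients to the same hemisphere or specific locations", which the article says makes the EEG signals more heterogeneous.

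**The concern.** After mirroring, the ipsilesional seed is the true C3 signal in left-lesion patients and the reflected C4 signal in right-lesion patients. In a right-handed sample the first serves the dominant hand and the second the non-dominant hand, and the paretic hand differs in the same way. Mirroring aligns patients by lesion side but leaves any left/right hemisphere difference in the data.

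The test named for coherence cannot take account of this. Any left/right difference enters the residual variance, and any chance imbalance in lesion side enters the estimated arm difference. Coherence carries the mechanism and biomarker aims, and a Bonferroni correction over many seed-to-region pairs leaves little precision to spare.

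**Working it through.** The plan gives no figure on this point. Its sample size concerns the Fugl-Meyer outcome and does not depend on the EEG analysis. For orientation, it reproduces: 2 × (1.960 + 1.282)² × 7.81² / 6.59² = 29.5, rounded up to 30 per group, with 70 enrolled after the dropout allowance.

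**Inputs**
- From the article: 70 patients allocated 1:1, taken as 35 per arm; 30 per arm as the evaluable number in 2.7.
- Assumed, because the article does not give them: the share *p* of left lesions, and the difference *g* in coherence between left- and right-lesion patients after mirroring, in within-side SDs.

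**1. Chance imbalance in lesion side.** Let the left-lesion counts in the two arms be independent Binomial(35, *p*).

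| *p* | P(counts differ by ≥ 5, i.e. 5/35 = 14 points) | P(differ by ≥ 7, i.e. 7/35 = 20 points) |
|---|---|---|
| 0.5 | 0.28 | 0.12 |
| 0.4 or 0.6 | 0.27 | 0.11 |

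If the total number of left lesions is instead held fixed (hypergeometric, 35 per arm), the answer depends heavily on that total, because the difference in counts can then only be odd or only be even:

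| Left lesions in 70 | P(≥ 5) | P(≥ 7) |
|---|---|---|
| 35 | 0.34 | 0.15 |
| 34 | 0.23 | 0.09 |
| 28 | 0.22 | 0.09 |

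The total is not known in advance, so the binomial figures are the ones to use.

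**2. Variance and power.** Pooling two sides that differ by *g* multiplies the within-arm variance by 1 + *p*(1 − *p*)*g*². With *p* = 0.5 this is 1 + 0.25*g*². Power uses the normal approximation, two-sided 5% before any Bonferroni correction, 30 per arm and an illustrative true effect of *d* = 0.8 within-side SDs. A 20-point imbalance shifts the arm difference by 0.20*g*.

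| *g* | Variance inflation | Power, side ignored | Shift at 20-point imbalance |
|---|---|---|---|
| 0 (or side removed) | 0% | 0.873 | 0 |
| 0.25 | 1.6% | 0.867 | 0.05 SD |
| 0.5 | 6.3% | 0.852 | 0.10 SD |
| 0.8 | 16% | 0.820 | 0.16 SD |
| 1.0 | 25% | 0.791 | 0.20 SD |

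**3. What is being compared.** Section 2.12.2.8 does not say whether the test uses post-treatment coherence or its change. For post-treatment values, *g* is the side difference in level. For change scores, a stable side difference cancels and *g* is only the side difference in change, so the lower rows of the table would be less likely.

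**The case against.** **The flip is correct for this seed.** M1 is defined by lesion status, so mirroring follows from the analysis and does what the article says: the lesion always lies on the same side. This stands, and the flip should stay.

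**The right-handedness rule is not wasted.** A reader might infer that the rule was meant to hold hemispheric dominance constant and that the flip undoes it. The documents do not support this. No purpose is stated for the rule, and restricting entry to right-handers is what allows lesion side to stand for dominant versus non-dominant hemisphere. A lesion-side covariate relies on that restriction.

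**The heterogeneity is disclosed and partly addressed.** Limitation (1) admits it, 2.16 plans EEG subgroups by infarct location, and the ANCOVA covariate list is open. A reader might infer that lesion side is wholly uncontrolled; that is too strong for the plan as a whole. But the article does not say that location includes hemisphere, subgroup results do not adjust the main arm comparison, and 2.12.2.8 names its own unadjusted test. It is unclear whether the ANCOVA in 2.16 reaches coherence at all.

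**This is detail for an analysis plan.** Covariates for an exploratory measure often are. Here, though, the article has fixed a test that cannot take a covariate, so the point concerns what is stated and not what is left out.

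**The size is unknown.** This stands. The article gives neither the left/right split nor a side effect on coherence, and at 0.25 to 0.5 SD the loss of power is small.

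**Conclusion.** The point holds as a low-cost improvement and not as an error. The stated coherence test ignores a factor that the article itself recognises as a source of EEG heterogeneity and that allocation does not balance by design.

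A reader might go further and infer bias or an internal contradiction. Neither is supported. Randomisation balances lesion side in expectation, and aligning by lesion is consistent with a seed defined by lesion. The primary Fugl-Meyer analysis and the sample size do not use the mirrored data.

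What remains is noise and possible chance imbalance in a non-primary EEG outcome. With 35 per arm and a 50% chance of a left lesion per patient, a difference of at least 5 left-lesion patients has probability about 0.28, and of at least 7 about 0.12. A side effect of 0.25 to 1.0 SD would add about 2% to 25% to the unadjusted variance. Both the split and the side effect are assumptions.

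**What to change.** 1. Keep the eligibility criterion and the flip.
2. In 2.12.2.8, replace the unadjusted t-test or Wilcoxon test with the ANCOVA already planned in 2.16: post-treatment coherence on arm, with baseline coherence and lesion side (left/right) as fixed covariates. Keep the Bonferroni correction. Baseline coherence will absorb much of any stable side difference, and the side term covers the rest.
3. In 2.16, state that the EEG subgroups by infarct location include hemisphere.

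The cost is a sentence in each section and one degree of freedom per model for lesion side. No new data are needed: side should be known from the CT or MRI used for inclusion, and baseline EEG is already scheduled. The trial is recruiting, so the change can still be specified before the database is locked.
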